### Recruitment {15}

Participant recruitment will occur weekly. A list of patients who are scheduled to have bariatric surgery will be provided by a staff member of the San Juan de Dios, Curicó’s Hospital, Chile. Participants who are interested and meet inclusion criteria will be invited to participate in the study after signing the informed consent.

## Assignment of interventions: allocation

### Sequence generation {16a}

#### Concealment mechanism {16b}

##### Implementation {16c}

After baseline assessment, randomization will be performed using sealed opaque envelopes. Envelopes will contain a piece of paper containing the letters A, B, or C, corresponding to the three groups of the current study. An independent researcher (i.e., not involved in the current study) will organize the envelopes in numerical order and will keep them in a safe place until baseline assessments are concluded. Then, the envelope labeled with the same number as assigned to the participants when they were included in the study will be unsealed and informed to the leading research. Participants could be assigned to one of the three groups: (1) control group, (2) moderate-intensity continuous training group, and (3) high-intensity interval training group. Figure 2 shows the study design flow chart describing all the steps of the study (Fig. 2).

**Fig. 2 Fig2:**
[figure not shown]
Study design flow chart

## Assignment of interventions: blinding

### Who will be blinded {17a}

This will be a single-blinded study where the outcome assessor (i.e., the researcher in charge of the evaluations) will have no information about the participants study group.

### Procedure for unblinding if needed {17b}

Not applicable, unblinding is not permissible in this trial.

## Data collection and management

### Plans for assessment and collection of outcomes {18a}

The assessments will be carried out at the institution’s Physical Medicine and Rehabilitation Service, and the intervention program will be carried out in the Service’s Adult Physical Therapy Gym. All the assessments will be conducted by a trained and experienced physical therapist (outcome assessor), which, prior the start of the study, was trained and familiarized with the evaluation protocol.

### Plans to promote participant retention and complete follow-up {18b}

A weekly phone call will be made to CG participants, asking about their health status and the indications for this group will be reinforced, in turn a text message will be sent to remind the evaluation date and time.

Participants who are in the training groups, in each session will be asked for feedback on their health status and will be sent a text message to remind them the training schedule.

In the event that any participant misses their training or evaluation, they will immediately proceed to call to ask about the reasons for not showing up.

### Data management {19}

All the information collected from this trial will always be protected and in the care of the lead research, who will assign a secure locker in his office where all documents of the investigation will be kept.

All electronic material will be duly stored and backed up in the researcher’s computer equipment with a safe password.

### Confidentiality {27}

In order to keep confidentiality after the assessments, the outcomes assessor will store the participants’ data separately from any identifying information and coded with a unique study ID. This ID will be linked to participant identity only within an encrypted, password-protected local database running on a secure host device maintained by outcome assessor and the study supervisor.

### Plans for collection, laboratory evaluation, and storage of biological specimens for genetic or molecular analysis in this trial/future use {33}

Not applicable, this trial does not have biological specimens.

## Statistical methods

### Statistical methods for primary and secondary outcomes {20a}

Data normality will be assessed with the Shapiro-Wilk test. Variance homogeneity and sphericity will be assessed with the Levene and Mauchly tests, respectively. For the primary and secondary outcomes that meet the assumptions for the analysis of variance (ANOVA), a mixed model ANOVA with Bonferroni correction will be used to assess the interaction between group (control group vs MICT vs HIIT) and time (baseline vs post 8-week intervention vs post 16-week intervention). Otherwise, data will be analyzed with the Wilcoxon test for within-group comparisons and the Mann-Whitney test for between-group comparisons using the Bonferroni’s correction. The significance level will be set at 5%. Cohen’s *d* will be calculated to determine the effect size. All analysis will be performed in SPSS 24.

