### Objectives {7}

This study will aim to determine the effect of MICT and HIIT programs on body composition, cardiopulmonary function, and perceived quality of life in bariatric surgery patients. We will also compare the effects of supervised exercise programs with those of standard follow-up. We hypothesized that both exercise programs would lead to greater improvement in the assessed outcomes than standard recommendations. Moreover, we expect the HIIT protocol to result in greater gains than MICT.

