### Sample size {14}

GPower 3.1 was used to determine the sample size, assuming a power of 80% and a significance level of 5%. Calculations were based on Herring et al. [37], considering BMI and heart rate as primaries outcomes. This study compared the effects of MICT versus a control group in patients post bariatric surgery. The higher sample size was obtained for the outcome “heart rate.” A total of 17 participants per group were required to detect a significant decrease in the heart rate (effect size = 1.01). However, due to possible dropouts, 25 participants will be included in each group, totaling 75 volunteers.

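### Bonferroni within each outcome is valid but needlessly conservative: Holm's step-down, over a stated family, rejects at least as much at the same 5% familywise error

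*Protocol article*

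**What the plan says.** All references are to the protocol article.

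- **Statistical methods {20a}, parametric route:** "a mixed model ANOVA with Bonferroni correction will be used to assess the interaction between group (control group vs MICT vs HIIT) and time". Time has three levels: baseline, 8 weeks and 16 weeks.
- **Same section, fallback route:** "data will be analyzed with the Wilcoxon test for within-group comparisons and the Mann-Whitney test for between-group comparisons", again with Bonferroni. The overall significance level is 5%. On neither route does the section give a divisor or say which comparisons form the family.
- **Objectives {7}:** "We hypothesized that both exercise programs would lead to greater improvement in the assessed outcomes than standard recommendations". HIIT is also expected to do better than MICT. For each outcome this makes three between-arm contrasts.
- **Sample size {14}:** "A total of 17 participants per group were required to detect a significant decrease in the heart rate (effect size = 1.01"), at 80% power and 5% significance. The effect comes from a two-group source: "This study compared the effects of MICT versus a control group in patients post bariatric surgery". After the dropout allowance, "25 participants will be included in each group, totaling 75 volunteers".

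**The concern.** Bonferroni compares every p-value with the same strict threshold, even after some hypotheses have already been rejected. Holm relaxes the threshold after each rejection and still controls the familywise error. With three arms a further gain is possible, because the pairwise hypotheses are linked: if one pair of arms differs, at most one of the other two pairs can be equal.

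The first objective says that both programmes are better than control, so it needs two rejections for an outcome. Bonferroni costs most in that situation. The trial may analyse as few as 17 per arm, and the avoidable loss falls on the trial's stated hypotheses. The article gives no reason for preferring the weaker method.

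**Working it through.** **1. Reproduce the plan's figure.** Inputs from the sample size section: d = 1.01, power 0.80, alpha 0.05. Two-sided testing is assumed, since sidedness is not stated. A two-sample t-test with noncentrality d·√(n/2) and 2n − 2 degrees of freedom gives n = 16.4, rounded up to **17 per group**, which matches. One-sided testing would give 13, which does not. The step from 17 to 25 allows for (25 − 17)/25 = 32% dropout.

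**2. Set out the rules for three arm pairs at one visit.** This family is an inference. With ordered p-values p(1) ≤ p(2) ≤ p(3), the thresholds are:

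| Rule | p(1) | p(2) | p(3) |
|---|---|---|---|
| Bonferroni | 0.05/3 = 0.0167 | 0.0167 | 0.0167 |
| Holm | 0.0167 | 0.05/2 = 0.025 | 0.05 |
| Shaffer (three arms) | 0.0167 | 0.05 | 0.05 |

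Holm and Shaffer stop at the first non-rejection. Their first threshold equals Bonferroni's and the later ones are larger, so neither can lose a Bonferroni rejection. For example, when p(1) ≤ 0.0167 and p(2) lies between 0.0167 and 0.025, Holm rejects a second pair and Bonferroni does not. The closed three-group procedure tests equality of all three arms at 5% and, if that is rejected, each pair at 5%.

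**3. Power for both programmes better than control.** Simulation assumptions: one outcome, change at one visit, SD 1, pooled error, control mean 0, both training arms at 1.01. The documents give no effect for HIIT, so equal effects are assumed.

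| Rule | 17 per arm | 25 per arm |
|---|---|---|
| Bonferroni | 53% | 78% |
| Holm | 60% | 83% |
| Shaffer | 69% | 89% |
| Closed | 71% | 90% |

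For a single training-versus-control contrast the figures, in the same order, are 68%, 71%, 76% and 78% at 17 per arm, and 87%, 89%, 92% and 93% at 25 per arm.

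**4. HIIT versus MICT, 25 per arm, MICT at 1.01.** The extra HIIT effect is assumed, so a range is shown.

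| Extra HIIT effect | Bonferroni | Holm | Shaffer |
|---|---|---|---|
| 0.3 SD | 9% | 17% | 18% |
| 0.5 SD | 26% | 40% | 42% |
| 1.01 SD | 87% | 94% | 94% |

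**5. Familywise error, one outcome at one visit.** With all arms equal: 4.3–4.4% for Bonferroni, Holm and Shaffer alike, since their first step is the same, and 5.0–5.1% for the closed test (nominally 5%; the excess is simulation error). With one pair equal and the third arm 1.01 SD away, at 25 per arm: about 1.6–1.7% Bonferroni, 4.0–4.1% Holm, and 4.9–5.0% Shaffer and closed.

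**6. Two post-baseline visits.** Suppose MICT equals control, HIIT is 1.01 SD better at both visits, and the between-visit correlation is between 0.3 and 0.7 (assumed). Three-arm test, then unadjusted pairs, done separately at each visit, gives a false MICT–control difference in 8.1–9.5% of trials at 17 per arm and 8.5–9.5% at 25. For two independent tests the figure would be 1 − 0.95² = 9.75%. Holm over all six pair-by-visit tests gave 3.5–3.7% in a check at an assumed correlation of 0.5. It holds 5% for any family and any correlation.

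**The case against.** The strongest reply is that Bonferroni is valid, pre-specified and simple, comes with matching simultaneous intervals, and in an exploratory pilot needs no refinement. At 25 per arm it still has about 86% power for one pair at the planning effect, using the two-group t-test at 0.05/3. All of that stands. A reader might infer that the plan's analysis is wrong or inflates error; the documents do not support that.

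Three other tempting readings also go too far.

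- **That the plan tests each pair at 5%/3.** The section gives no divisor. The family could be arm pairs, time pairs, both, or could include the within-group Wilcoxon tests. The power figures depend on the arm-pair reading; Holm's advantage over Bonferroni does not.
- **That the three-arm test followed by unadjusted pairs can simply replace Bonferroni.** It holds 5% only for one test per pair. The plan has two post-baseline visits, and its rank route names no three-group test as a first step.
- **That a better correction restores the planned power.** With 17 per arm even the closed test reaches only 78% for one contrast.

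It is also fair to say that control across the trial is loose, not strict: there are four primary domains and no stated adjustment across them. If these were independent, the chance of any false positive would be about 1 − (1 − 0.044)⁴ ≈ 16% with Bonferroni within each outcome and 1 − 0.95⁴ ≈ 19% with the closed test. With every arm equal, Holm leaves this where Bonferroni has it, which favours Holm as the default.

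**Conclusion.** The point holds as an efficiency improvement and not as an error in the plan. For any family within an outcome, Holm is at least as powerful as Bonferroni at the same 5% familywise level.

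If the family is the three arm pairs at one visit, the gain in showing both programmes better than control at an effect of 1.01 is 7 points with Holm (53% to 60%) and 16 with Shaffer (to 69%) at 17 per arm. At 25 per arm it is 5 points (78% to 83%) and 11 points (to 89%). These sizes assume two-sided tests, equal SDs, a single-visit contrast and equal effects of the two programmes.

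The point does not address multiplicity across the primary domains, or a sample size computed at an unadjusted 5%.

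**What to change.** In the statistical methods section {20a}, replace the Bonferroni correction on both routes by:

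> Holm step-down correction over the between-group comparisons made for each outcome (three arm pairs at each post-baseline visit analysed).

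This also states the family. If both visits are tested, the family has six members and Holm starts at 0.05/6 = 0.0083. If the authors had meant three pairs per visit, starting at 0.0167, some of the gain then goes on covering the second visit. Naming one visit for the between-group tests avoids that.

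Shaffer, or the closed procedure (Kruskal-Wallis as the first step on the rank route), is acceptable for one pre-named contrast only, such as change from baseline to the post-16-week assessment.

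The cost is one sentence, with no extra participants or data. Holm needs only the unadjusted pairwise p-values and no global test. The downside is that simple simultaneous confidence intervals are lost, so ordinary 95% intervals should be reported for each pair.

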**Discussion:**

Both exercise protocols in this study were developed according to evidence-based practice. It is expected that, after 16 weeks of intervention, body composition (measured by electrical bioimpedance), cardiopulmonary function (measured by heart rate variability, maximal inspiratory pressure, maximal expiratory pressure, peak expiratory flow, handgrip strength, and the 6-min walk test), and perceived quality of life (measured by the Moorehead-Ardelt quality of life questionnaire II and bariatric analysis and reporting outcome system scores) will improve, especially in the HIIT group.

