### Outcomes {12}

Outcomes will be assessed at four time points: (1) 1 week before surgery, (2) 21 days after surgery (baseline before starting the exercise program), (3) 8 weeks after the beginning of the exercise program, and (4) 1 week after the end of intervention.

Primary outcomes will be (1) body composition, (2) heart rate variability, (3) 6-min walk test results, and (4) perceived quality of life. Secondary outcomes include the results for (1) maximal respiratory pressure, (2) flowmeter, (3) hand dynamometry, (4) the 30-s sit-to-stand test, and (5) the basal metabolic rate.

Data collection will include sex, age, place of residence, marital status, education level, and physical activity level according to the International Physical Activity Questionnaire [29].

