## Discussion

The objective of this study will be to investigate the effects of 16 weeks of MICT and HIIT on body composition, cardiopulmonary function, and perceived quality of life in bariatric surgery patients.

MICT has been proven effective for increasing fat mass loss and decreasing lean mass loss after bariatric surgery, as well as for improving control of glucose homeostasis and cardiovascular capacity [21, 22]. On the other hand, HITT protocols, which involve repeating intense efforts that last a few seconds separated by short periods of recovery, have shown to promote beneficial changes in patients with lifestyle-induced chronic diseases [38]. Also, HIIT improves cardiorespiratory fitness and insulin sensitivity in obese patients and is well tolerated by overweight and insulin-resistant people [25–27]. However, to the best of our knowledge, no studies have compared MICT and HITT protocols in bariatric surgery patients.

It should be also pointed out that besides relevant outcomes, such as body composition and functional capacity, this study consider the assessment of the cardiac autonomic control, which will provide important information about the effectiveness of both methods in a cardiovascular marker related to the risk of cardiovascular events and mortality [39, 40]. Determining which exercise strategy better suits this population and is more effective regarding these outcomes is relevant for bariatric surgery management and formulating recommendations.

Another strength of our study is the presence of a control group that follows current Chilean recommendations after bariatric surgery. If our hypothesis is confirmed, this exploratory pilot trial could be a start point to new recommendations about supervised exercise after bariatric surgery.

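### The only parametric test named is a group-by-time interaction over baseline, week 8 and week 16; no end-of-training contrast is fixed, so week 8 alone could be read as a 16-week effect

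*Protocol article*

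**What the plan says.** The section on statistical methods {20a} states that "a mixed model ANOVA with Bonferroni correction will be used to assess the interaction between group (control group vs MICT vs HIIT"). The second factor in that interaction has three levels, one of them at mid-programme; it is given as "time (baseline vs post 8-week intervention vs post 16-week intervention"). This applies to all primary and secondary outcomes that meet the ANOVA assumptions. Other outcomes go to Wilcoxon tests within groups and Mann-Whitney tests between groups, also Bonferroni-corrected. Neither route names a deciding visit or a specific between-arm contrast.

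The time frame of the question is set elsewhere. The discussion part of the abstract opens with "It is expected that, after 16 weeks of intervention, body composition", then lists further outcomes expected to improve, most of all under HIIT. The main Discussion gives the objective as to "investigate the effects of 16 weeks of MICT and HIIT on body composition" and the other outcome domains.

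The Objectives section {7} states the hypothesis without a time point: "We hypothesized that both exercise programs would lead to greater improvement in the assessed outcomes than standard recommendations", with HIIT expected to do better than MICT. Outcomes {12} lists four assessments, of which the two after the start of training are "3) 8 weeks after the beginning of the exercise program, and (4) 1 week after the end of intervention"; neither is ranked above the other. The last of these, visit 4 below, is evidently what the analysis section calls post 16 weeks.

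**The concern.** Three arms by three times gives an interaction with (3 − 1)(3 − 1) = 4 degrees of freedom. It is sensitive to any difference between arms in the shape of the time course. It can therefore be significant when the arms are identical at baseline and at visit 4 and differ only at week 8. It also does not say which arms differ.

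The questions the article wants answered are directional and concern the end of training: each exercise programme against standard recommendations, and HIIT against MICT. The post-trial care provision {30}, which offers participants the training with the best effect, likewise needs to know which arm did better. With no visit-4 contrast fixed, the choice of what to report as the answer is left until the data are in, and a week-8 difference may be taken as support for a 16-week effect that is absent.

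**Working it through.** **The plan's own figure.** Sample size {14} gives 17 per group for an effect size of 1.01, 80% power and a 5% level. A two-sided two-sample t-test with n = 17 per group has noncentrality 1.01 × √(17/2) = 2.94 and power 81.5%; n = 16 gives 78.9%. The 17 reproduces, but as a two-group comparison and not as a 3 × 3 interaction.

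**Inputs.** From the article: 3 arms, 3 analysed times, 25 per arm, 5% level. Assumed, because the article gives none of these: SD 1 at every visit, equal correlation r between visits (compound symmetry) of 0.5 or 0.7, no dropout, and the mean profiles below.

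**Formulas** (noncentral F, n per arm):
- Interaction: λ = n × SS_int / (1 − r), where SS_int is the sum of squared double-centred cell means; df 4 and 6(n − 1) = 144.
- Change from baseline to visit 4: λ = n × SS_4 / [2(1 − r)], where SS_4 is the sum of squared centred arm means at visit 4; df 2 and 72.
- Visit 4 adjusted for baseline (ANCOVA): λ ≈ n × SS_4 / (1 − r²); df 2 and 71.

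**Week-8-only effect.** HIIT is 0.5 SD better at week 8 and every other cell is equal. SS_int = 0.25 × (2/3) × (2/3) = 0.111.
- r = 0.5: λ = 25 × 0.111 / 0.5 = 5.56, so the interaction is significant in 42% of trials.
- r = 0.7: λ = 25 × 0.111 / 0.3 = 9.26, giving 66%.
- Either visit-4 test: SS_4 = 0, so 5%.

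A simulation (10,000 trials per scenario, 25 per arm, r = 0.5 or 0.7, compound symmetry or AR(1)) with 0.8 SD in both exercise arms at week 8 only gave 82% to 98% for the interaction and about 5% for the visit-4 tests.

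**Real 16-week effect.** MICT 0.4 SD and HIIT 0.8 SD at visit 4, so SS_4 = 0.16 + 0 + 0.16 = 0.32. If half of this is present at week 8, SS_int = 0.32 × 0.5 = 0.16. If it is fully present at week 8 (sustained) or not yet present (late), SS_int = 0.32 × 2/3 = 0.213.

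| r | Time course | Interaction: λ, power | Change score: λ, power | ANCOVA: λ, power |
|---|---|---|---|---|
| 0.5 | Gradual | 8.00, 59% | 8.00, 70% | 10.67, 82% |
| 0.5 | Sustained or late | 10.67, 73% | 8.00, 70% | 10.67, 82% |
| 0.7 | Gradual | 13.33, 83% | 13.33, 90% | 15.69, 94% |
| 0.7 | Sustained or late | 17.78, 93% | 13.33, 90% | 15.69, 94% |

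Under gradual build-up the interaction and the change score have the same λ, and the interaction loses only because it spreads it over 4 degrees of freedom instead of 2. Under a sustained or late effect its λ is larger, which slightly more than offsets this.

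**Sensitivity to the correlation structure.** The same simulation under AR(1) with r = 0.7, 25 per arm and both exercise arms 0.8 SD better at visit 4 gave, for interaction, change score and ANCOVA:
- gradual: 79.7%, 81.7% and 91.4%;
- sustained: 92.4%, 81.2% and 91.3%;
- late: 91.8%, 81.3% and 91.0%.

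**The case against.** Four points on the other side have force.

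- **No success rule is stated.** A reader might infer that a significant interaction counts as success. The article says only that the ANOVA will assess the interaction, and it calls the trial an exploratory pilot. It does speak of the hypothesis being confirmed and of a starting point for new recommendations, but that is not a decision rule. The risk is one of interpretation.
- **The time point is not firmly fixed.** The formal hypothesis names none, and the wording in the main Discussion can be read as programme length. Only the abstract's expectation is clearly dated to 16 weeks. This stands, but it supports naming a deciding visit.
- **Follow-up comparisons are implied.** A Bonferroni correction has no natural use for a single omnibus F, so pairwise comparisons are probably intended; Cohen's d and the Mann-Whitney fallback also compare groups. These could locate a difference. But the article does not say which pairs or which visit, and comparisons at both visits would still let week 8 carry a claim.
- **The week-8-only scenario is extreme.** It requires a benefit to vanish while supervised training continues and HIIT volume is still being raised. This is fair: the 42% and 66% show what the test can respond to and do not forecast what will happen.

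A reader might also infer that the planned test is generally the weaker one for a 16-week effect. The calculations do not support that: against a change-score test it is weaker for gradual build-up and stronger for sustained or late effects.

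**Conclusion.** The point holds in a limited form. The article fixes an omnibus test over three times and no end-of-training between-arm contrast, while its stated expectation and objective refer to 16 weeks. A significant interaction therefore does not by itself show a 16-week effect: under the assumed week-8-only effect of 0.5 SD it occurs in 42% to 66% of trials with identical arms at visit 4.

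No general loss of power can be claimed. Against a change score the difference runs from 11 points lower (59% versus 70%) to 3 points higher (73% versus 70%) at r = 0.5. The baseline-adjusted visit-4 test is ahead of the interaction in every compound-symmetry scenario tabulated, by 9 to 24 points at r = 0.5 and by 1 to 11 points at r = 0.7. Under AR(1) at r = 0.7 that advantage disappears for sustained or late effects.

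All these figures rest on assumed SDs, correlations and time courses. For an exploratory pilot this is a clarification that should be made; it does not invalidate the analysis.

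**What to change.** In the statistical methods section {20a}, state that for each outcome the deciding comparison is the between-arm difference at visit 4 adjusted for the day-21 baseline value, by ANCOVA or by the equivalent visit-4 contrast in the mixed model. Bonferroni-corrected pairwise arm contrasts (MICT versus control, HIIT versus control, HIIT versus MICT) follow. Describe the week-8 results and the group-by-time interaction as supportive, showing the time course only. The rank-based fallback should name the same visit.

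BAROS has no day-21 value, because the section on perceived quality of life applies it only at the final evaluation. For it, compare the arms at visit 4 without that adjustment.

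The change costs a few sentences and uses the same data and software. The price is that week-8 results can no longer carry a claim by themselves.

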#### Heart rate variability

R-R intervals will be recorded with a Polar V800 heart rate monitor (Polar, Oi, Finland); a sensor will be placed on the chest at the fifth intercostal space. The participant will then rest in the supine position for 10 min to stabilize heart rate and blood pressure. R-R intervals will be recorded under the following conditions: (1) after resting in the supine position for 10 min and (2) after resting in the orthostatic position for 10 min (active standing). The participants’ respiratory rate will be recorded throughout the test.

Heart rate variability will be analyzed through spectral analysis in an autoregressive model. The spectral components will be obtained at low frequency (LF, 0.04–0.15 Hz) and high frequency (HF, 0.15–0.4 Hz) bands in absolute units (ms^2^). Standardized units are calculated as the ratio between LF or HF (absolute units) and the power spectral density, minus the very low frequency component (VLF, 0.003–0.04 Hz) and multiplied by 100. The LF band is modulated by the sympathetic and parasympathetic autonomic nervous system (with sympathetic predominance), the HF band is associated with cardiac vagal control, and the LF/HF ratio is calculated to assess sympathovagal balance [30].

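### Assumption checks on the trial data choose each outcome's test, and the fallback states no between-group comparison of change; one baseline-adjusted model would answer the question with more power

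*Protocol article*

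**What the plan says.** The objectives (Protocol article, Objectives {7}) are comparative: "We will also compare the effects of supervised exercise programs with those of standard follow-up". The same section hypothesizes that both programs will improve outcomes more than standard recommendations, and HIIT more than MICT. These are differences between arms in change.

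Statistical methods {20a} starts with assumption checks: "Data normality will be assessed with the Shapiro-Wilk test", then Levene for equal variances and Mauchly for sphericity. Outcomes that meet the ANOVA assumptions get a mixed ANOVA with a group-by-time interaction, where baseline, week 8 and week 16 are the three levels of time. For all others, "data will be analyzed with the Wilcoxon test for within-group comparisons and the Mann-Whitney test for between-group comparisons", with a Bonferroni correction. The text does not say whether Mann-Whitney is applied to follow-up values or to changes. Neither route names a baseline covariate, and the section on additional analyses {20b} plans none.

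Heart rate variability is a primary outcome. Its section says "The spectral components will be obtained at low frequency" and high-frequency bands in absolute power units, and it adds normalized units and the LF/HF ratio.

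**The concern.** Two outcomes in the same trial can end up answering different questions, depending on how their data happen to look. One that passes the checks is tested for a difference between arms in change. One that fails gets a within-arm test of change, which compares no arms, and a between-arm test whose variable is not stated. If that variable is the follow-up value, the baseline measurement goes unused.

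Two things are at stake. One is power in a small trial. The other is interpretation: with three separate within-group Wilcoxon tests, it is easy to report that one arm improved and another did not as though that showed a treatment effect.

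**Working it through.** **Inputs from the protocol.** Sample size {14}: "assuming a power of 80% and a significance level of 5"%; "A total of 17 participants per group were required to detect a significant decrease in the heart rate (effect size = 1.01"); "due to possible dropouts, 25 participants will be included in each group, totaling 75 volunteers". Statistical methods {20a}: "The significance level will be set at 5"%. Sidedness is not stated.

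**Assumed inputs.** The protocol gives no baseline-to-follow-up correlation (rho), so 0.3 to 0.8 is shown. The only effect size it gives is 1.01, for heart rate; a smaller d = 0.5 SD of the follow-up value is used for illustration. Equal SDs at baseline and follow-up and a two-sided 5% level are assumed. No Bonferroni factor is applied, because the family is not defined.

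**Step 1: reproduce the plan's figure.** A two-sample t test with d = 1.01, two-sided 5% and 80% power gives n = 16.4, rounded up to 17 per group (power 81.5%). The stated 17 is reproduced, and it comes from a two-group comparison without a covariate.

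**Step 2: how often would the switch operate by chance?** The protocol does not say how the checks are applied. Suppose each of the nine group-by-time cells gets a Shapiro-Wilk test at 5%, with three Levene tests and one Mauchly test, and any rejection diverts the outcome.
- Nine independent Shapiro-Wilk tests: 1 − 0.95^9 = 37% chance of at least one false rejection.
- All 13 checks, if independent: 1 − 0.95^13 = 49%.
- Simulation with truly normal, spherical data: 46% at 17 per arm and 50% at 25 per arm.

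**Step 3: precision of the between-arm contrast.** With the follow-up SD set to 1, the residual SD is 1 for follow-up values alone, √(2(1 − rho)) for change and √(1 − rho²) for ANCOVA. The change contrast therefore needs 2(1 − rho)/(1 − rho²) = 2/(1 + rho) times the ANCOVA sample: 2/1.5 = 1.33 at rho 0.5, 2/1.7 = 1.18 at 0.7 and 2/1.8 = 1.11 at 0.8.

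Power at 25 per arm, d = 0.5. The change-score t test and ANCOVA columns apply the two-sample t formula to d divided by the residual SD; the Mann-Whitney columns are simulated.

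| rho | Mann-Whitney, follow-up | Mann-Whitney, change | t test, change | ANCOVA |
|---|---|---|---|---|
| 0.3 | about 38% | not run | 31% | 44% |
| 0.5 | 38% | 39% | 41% | 52% |
| 0.7 | 38% | 59% | 61% | 68% |
| 0.8 | 38% | 75% | 78% | 82% |

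Separate simulation of the last two columns gave 32/40/61/78% and 44/51/69/82%, the same within simulation error. Follow-up values alone do not depend on rho.

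**Step 4: type I error.** With no true difference, every between-arm method stayed near 5% in simulation (4.2% to 5.4%).

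**Step 5: disagreement of within-arm tests.** Suppose all three arms have the same true change, and each Wilcoxon test has power p. The chance that the three verdicts are not all alike is 1 − p³ − (1 − p)³ = 3p(1 − p), which cannot exceed 75%. At 25 per arm and a 5% level, with the common change in SDs of the change score:
- no change: about 13%
- 0.4 SD (p about 0.47): about 75%
- 0.6 SD (p about 0.80): about 49%
- 0.8 SD (p about 0.96): about 10%
- 1.0 SD: 1% to 2%

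**The case against.** **The fallback could be read as sound.** Mann-Whitney on change scores would compare change between arms, which is the stated hypothesis, and would lose little against the t test (59% against 61% at rho 0.7). This stands: a reader might infer that the fallback cannot test the hypothesis, but the text only leaves the variable open. What remains is that the between-arm test is not tied to change, and no other planned analysis restores that comparison.

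**The ANOVA route does use baseline.** Baseline is a level of time, so the interaction compares change from baseline. A reader might infer that this route ignores baseline; it does not. It lacks only a baseline covariate, which costs precision and not validity.

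**Within-arm tests are not offered as treatment comparisons.** The protocol lists a separate between-group test. A reader might infer that the plan inflates false claims of benefit, but the between-arm tests hold their level. Chance disagreement between arms is frequent for modest common changes and nearly disappears for large ones, which may be the case for body composition after surgery.

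**The power figures rest on assumptions.** This also stands. At the protocol's own d = 1.01 with 25 per arm, a t test on follow-up values already has 94% power, so the loss matters mainly for smaller effects. At rho 0.3, change scores do worse than follow-up values. ANCOVA had the highest power at every correlation examined.

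**Skewed heart rate variability is not documented.** The protocol gives no distribution. That spectral power and LF/HF may be skewed is an assumption based on their being positive quantities. The trigger is also wider than normality: unequal variances or failed sphericity would divert an outcome too.

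**Conclusion.** The concern holds in a limited form. The analysis is chosen outcome by outcome from assumption checks on the trial data, and the fallback, as written, states no between-group comparison of change and no baseline term in the between-group test. It therefore does not clearly test the stated hypothesis.

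If Mann-Whitney is run on follow-up values, the cost at d = 0.5 and 25 per arm is about 38% power against roughly 44% to 82% for ANCOVA as rho runs from 0.3 to 0.8. The valid ANOVA route gives up less: its change contrast needs 1.33 times the ANCOVA sample at rho 0.5 and 1.18 times at 0.7. These sizes depend on the assumed d and rho. Nothing here invalidates a between-arm test or changes the planned sample size. The improvement is worth making because the baseline is already measured.

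**What to change.** Remove the pre-test switch. For every outcome measured at baseline, prespecify one model (ANCOVA or a linear mixed model) of the week-8 and post-16-week values on group, visit and group-by-visit, with the 21-day postoperative value as covariate. Report pairwise adjusted differences with 95% confidence intervals at the final visit. BAROS is applied only at the final evaluation, so it needs its own stated between-group comparison.

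State in advance that heart rate variability power and LF/HF will be log-transformed. Check model residuals; if they are poor, keep the same contrast and use bootstrap intervals or rank ANCOVA. Label within-group tests as descriptive and not as evidence of a treatment effect.

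This changes analysis wording only. It needs no new data or participants, the main model runs in the SPSS release already named, and there is no material downside.
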